#### 2.3.5. Sample Size Justification

It can be assumed that the effects in persons with PPA are comparable to the effect sizes in persons with aphasia after stroke, as the impairment patterns are similar [42], and many approaches for the treatment of poststroke aphasia are successfully transferable to PPA [6,47]. Based on the results of Corsten et al. (2015), who reported an 85.19% improvement in Complaints and an 88.89% improvement in Burden score on the Aachen Life Quality Inventory [23] from baseline to follow-up, with an overall low to moderate effect size (d = 0.22 to 0.58) [19], an a priori power analysis was conducted using G*Power 3.1.7. This resulted in a total sample size of 24 for an estimated effect size of f = 0.275 (d = 0.55; α = 0.05; power = 0.8). It is assumed that with this sample size, effects can be detected in persons with PPA who are examined with the Stroke and Aphasia Quality of Life Scale-39 (SAQOL-39, [48]). It is possible that the effect sizes in persons with PPA are even greater if persons with mild depression are included; thus, a lower baseline score for QoL can be expected.

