This study is emphasised as the one with the highest quality and level of evidence for persons with poststroke aphasia and demonstrates the effects of the biographic-narrative approach narraktiv [18,19]. The narraktiv intervention contains five individual and seven group therapy sessions in which biographic storytelling is stimulated. This approach is based on the idea that aphasia hinders the natural and daily redevelopment of identity, as the medium for identity work (communication) is impaired. Disturbed identity work leads to a negative self-image and thus reduces QoL. Supporting narration can help persons with aphasia to work on their identity and to build a sense of coherence, ultimately improving their QoL [9,20,21]. The participants in the narraktiv intervention were persons with poststroke aphasia who did not have depression or who exhibited early signs of depression. Significant improvements with small to medium effect sizes were observed in improvement of mood and health-related QoL, measured by the Visual Analogue Mood Scale (VAMS, [22]) and the Aachen Life Quality Inventory [23]. The effects remained stable over a period of three months after the intervention or even increased towards follow-up, as in the case of the Aachen Life Quality Inventory scores. Since many therapeutic approaches can be transferred from persons with poststroke aphasia to persons with PPA [6], it seems promising to apply the concept of the biographic-narrative approach narraktiv according to Corsten et al. (2015) to persons with PPA.

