#### 2.3.4. Randomisation

The division of the participants into groups is necessary for conducting the efficacy study and will be carried out as a random allocation by the deputy study director ([name]) [46]. Since the therapy groups will consist of six participants, four blocks must be formed (N = 24). A permutation of the four blocks will be drawn at random, with the first half (*n* = 12) of the permutation being assigned to the therapy group and the second half (*n* = 12) assigned to the waiting group (see Figure 4). Each allocation thus applies to six consecutive participants. Groups will be randomised without balancing.

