#### 2.4.3. Data Analysis

Qualitative data analysis will be carried out using MAXQDA (VERBI Software, 1989–2021); quantitative data analysis will be carried out using the statistical software SPSS (version 27, IBM^®^) and RStudio (2023.09.1 Build 494).

The data from ‘phase one’ will be analysed via qualitative content analysis by Elo and Kyngäs (2008, [62]). The video material of the focus group interview will be transcribed according to the content semantic transcription by Dresing and Pehl (2018) by two SLTs [63]. The coding process will be carried out by two SLTs. Categories will be formed deductively. The category system for the analysis will contain categories such as ‘characteristics of good therapy’/‘Augmentative and Alternative Communication’/‘coping strategies’/‘opinion on therapy materials’.

The quantitative data of ‘phase two’ will be analysed descriptively and inferentially. Before the inferential analysis, the normal distribution will be checked in both groups using the Shapiro–Wilk test in conjunction with a Q–Q plot and values of skew and kurtosis [64]. For the primary outcome of QoL, analysis of variance (ANOVA) will be used to calculate the point and mean values (before–after and therapy-waiting group comparisons). In addition, the dependent structure of the data will be examined using the intraclass correlation coefficient (ICC). To analyse the individual cases, the critical difference between the test procedures used will be determined. Recruitment, participation, fidelity, and reasons for drop-outs or missing data will be documented using descriptive statistics.

Semistructured interviews of ‘phase two’ will also be transcribed according to the content semantic transcription by Dresing and Pehl (2018, [63]) and analysed according to the qualitative content analysis by Elo and Kyngäs (2008, [62]). The category system for the analysis will contain categories such as ‘general conditions’, ‘content’, ‘materials’, ‘evidence of improvements in QoL’, or ‘evidence of identity work’.

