#### 2.4.5. Criteria for Success

The criteria for success of ‘phase two’ are defined as follows:Significant improvement in SAQOL-39 score with a medium effect size from pre- to post-intervention.Improvements in SAQOL-39 score between t0 and t1 are significantly greater in the therapy group than in the waiting group.In the semistructured interviews, the participants report generally positive perceptions about the acceptability of the intervention.The fidelity rate is at least 80% in the random sample evaluated by independent rater.Stable values or improvements on the MADRS.Stable values or improvements on the VAS.

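### The 80% power stated for N = 24 does not carry over to the randomised success criterion, the therapy versus waiting difference in SAQOL-39 change from t0 to t1

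*Protocol article*

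**What the plan says.** Section 2.3.5 (Sample Size Justification) says that "an a priori power analysis was conducted using G*Power 3.1.7" and that it gave "a total sample size of 24 for an estimated effect size of f = 0.275 (d = 0.55; α = 0.05; power = 0.8"). It does not name the test, the number of measurements, the correlation between measurements or the sidedness. It concludes that effects measured with the SAQOL-39 can be detected at this size. The planning effect comes from the earlier narraktiv study in post-stroke aphasia, where the change ran "from baseline to follow-up, with an overall low to moderate effect size (d = 0.22 to 0.58"). The Introduction adds that the effects in that study stayed stable after the intervention "or even increased towards follow-up, as in the case of the Aachen Life Quality Inventory scores".

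Section 2.4.5 (Criteria for Success) sets two significance requirements on the SAQOL-39:
- Pre-post: "Significant improvement in SAQOL-39 score with a medium effect size from pre- to post-intervention".
- Between arms: "Improvements in SAQOL-39 score between t0 and t1 are significantly greater in the therapy group than in the waiting group".

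Section 2.4.3 (Data Analysis) covers both: "analysis of variance (ANOVA) will be used to calculate the point and mean values (before–after and therapy-waiting group comparisons"). Section 2.3.4 assigns the first 12 to therapy and "the second half (*n* = 12) assigned to the waiting group". Section 2.3.3 treats the waiting group after 10 weeks, and Section 2.4 places the assessments 10 weeks apart. So t0 to t1 is the only interval with an untreated control.

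**The concern.** One sample size figure stands behind two quite different tests. The pre-post test can use each of the 24 participants as their own control. The between-arm test compares 12 changes with 12 changes and is much less precise.

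The step f = d/2 (0.275 = 0.55/2) is correct for a main effect with two levels. It is not correct for a group-by-time interaction, which is what the between-arm criterion tests. A reader of Section 2.3.5 will take the 80% to cover both criteria.

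At stake is how a non-significant between-arm result is read. If the real chance of significance is well below 80% even when the therapy works as assumed, such a result says little about inefficacy. In a rare disease, a wrong reading would be hard to correct with a second trial.

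**Working it through.** **Inputs.** From the article: N = 24, 12 per arm, f = 0.275, d = 0.55, alpha = 0.05. Assumed, because the article gives no figure: two-sided testing, a t0–t1 correlation ρ of 0.5 to 0.8, and no drop-out or clustering. SD means the SD of the raw SAQOL-39 score unless the SD of change is named.

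**1. Reproducing N = 24.** The G*Power repeated-measures formula is λ = f²·N·m/(1 − ρ), with (g − 1)(m − 1) and (N − g)(m − 1) degrees of freedom, for g groups and m measurements. Two settings with two groups give a minimum N of 24:
- m = 3, ρ = 0.5: λ = 0.075625 × 24 × 3/0.5 = 10.89; power 0.82.
- m = 2, ρ = 0.6: λ = 0.075625 × 24 × 2/0.4 = 9.075; power 0.82.

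With m = 2 and ρ = 0.5, λ = 7.26 and power at N = 24 is 0.73. So 24 is a reproducible figure, but the article does not show which setting produced it.

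**2. What f = 0.275 means for the interaction.** Let δ be the between-arm difference in mean change, in SD. In a 2 × 2 layout the interaction terms of the four cells are ±δ/4, so f = δ/4.
- f = 0.275 gives δ = 4 × 0.275 = 1.10 SD, which is 2 × 0.55.
- δ = 0.55 gives f = 0.55/4 = 0.1375.

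Cross-check at ρ = 0.5: a t test on change with δ = 1.10 and SD of change 1 has squared noncentrality 1.10² × 12/2 = 7.26, the same λ as in step 1.

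**3. Power of the between-arm criterion.** SD of change = √(2(1 − ρ)); standardised difference = δ/SD of change; noncentrality = that difference × √(12/2), with 22 df. The third column takes therapy gain 0.55 and waiting arm unchanged (δ = 0.55). The fourth adds an illustrative waiting-arm decline of 0.2 (δ = 0.75). The last is the pre-post test of step 4.

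| ρ | SD of change | δ = 0.55 | δ = 0.75 | Pre-post, all 24 |
|---|---|---|---|---|
| 0.5 | 1.000 | 25% | 42% | 73% |
| 0.6 | 0.894 | 30% | 50% | 82% |
| 0.7 | 0.775 | 38% | 62% | 91% |
| 0.8 | 0.632 | 53% | 79% | 98% |

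At δ = 0.55, power is 65% at ρ = 0.85 and 82% at ρ = 0.9. At ρ = 0.5, 80% power needs 53 per arm; at ρ = 0.8 it needs 22. At the ends of the cited range, over ρ = 0.5 to 0.8, δ = 0.22 gives 8% to 13% and δ = 0.58 gives 27% to 57%. One-sided testing at δ = 0.55 gives 37% to 66%.

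**4. Power of the pre-post criterion.** A paired test in all 24 with a change of 0.55 SD has noncentrality (0.55/SD of change) × √24, with 23 df. The last column of the table shows 73% to 98%. This assumes that both arms are pooled, which Section 2.4.5 does not say.

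**5. Precision of the between-arm comparison.** In SDs of the change score, 12 versus 12 has 80% power for a difference of 1.20. The 95% CI half-width is t(0.975; 22) × √(2/12) = 2.074 × 0.408 = 0.85. In raw SD the half-width is 0.85 at ρ = 0.5 and 0.85 × 0.632 = 0.54 at ρ = 0.8.

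**6. Clustering.** Therapy is given in groups of six. With an assumed intraclass correlation of 0.05 the design effect is 1 + 5 × 0.05 = 1.25. Power at δ = 0.55 then falls to about 21% to 45%, before any loss of degrees of freedom from having only four groups.

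**The case against.** The strongest reply is that Section 2.3.5 never ties its 80% to the between-arm criterion. The planning effect is a change from baseline to follow-up, so the pre-post criterion, listed first in Section 2.4.5, is its natural target, and there N = 24 is adequate or close to it. This stands as far as it goes. It does not rescue the general statement that effects can be detected, because Section 2.4.5 also requires significance between the arms.

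A second reply is that the inputs are unknown. PPA is progressive, so the waiting arm may decline and enlarge the contrast, and Section 2.3.5 argues that effects may be larger in this population. That is fair, and it is why the power is given as a conditional range. Even the illustrative 0.2 SD decline stays below 80% up to a correlation of 0.8.

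Three stronger readings are tempting, but the documents do not support them:
- *That 24 is miscalculated, or was computed for three measurements instead of two.* Two measurements with a correlation of 0.6 give the same N, so the setting cannot be inferred.
- *That the article expressly claims 80% power for the t0 to t1 comparison.* It names no test.
- *That the source effect was uncontrolled.* The article mentions no control group for it but does not say there was none. It does say that it is a baseline-to-follow-up effect, that 0.55 lies near the top of the cited range, and that scores on that scale rose towards follow-up. This gives reason for caution in using 0.55 for a contrast at t1.

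**Conclusion.** The point holds in this form: the stated power does not apply to the randomised SAQOL-39 criterion at the stated effect. The f-to-d mismatch needs no assumption about software settings. As an interaction effect, f = 0.275 is 1.10 SD, not 0.55 SD.

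The size of the shortfall is conditional. Power is about 25% to 53% if the difference in change is 0.55 raw SD, the waiting arm is unchanged, testing is two-sided and the t0–t1 correlation is 0.5 to 0.8. If 0.55 was standardised by the SD of change, power is 25% whatever the correlation. The documents give neither the correlation nor the standardiser. What can be said with confidence is that power is below 80% unless the correlation is near 0.9 or the waiting arm declines appreciably, and that clustering and drop-out would lower it further. N = 24 can roughly support the uncontrolled pre-post criterion, but not the controlled one.

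**What to change.** Keep N = 24 and restate Section 2.3.5:
- Name the test behind the stated figure, and give power separately for the two SAQOL-39 criteria.
- For the pre-post criterion, say whether both arms are pooled and which SD standardises d.
- For the between-arm t0 to t1 comparison, state the assumed correlation and waiting-arm change, the resulting power range, the detectable difference (about 1.2 SD of the change score) and the 95% CI half-width (about 0.85 SD of the change score). Say that these are before clustering and drop-out.
- Limit the statement that effects can be detected to what these figures support.
- Commit to reporting the between-arm effect with its 95% CI, and add to Section 2.4.5 that a non-significant between-arm result is not by itself evidence of inefficacy.

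The cost is a less favourable stated power and a short revision of the text. No extra patients or assessments are needed.

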### 2.4. Measurements

All participants enrolled in ‘phase two’ will be assessed through self-assessments and external assessments at four test times (t0, t1, t2, t3) every 10 weeks.

#### 2.4.1. Measuring Instruments

The primary outcome of QoL will be measured quantitatively by using the SAQOL-39 [48]. The SAQOL-39 is a feasible, reliable and valid assessment of health-related QoL in persons with chronic poststroke aphasia [48]. There is an international consensus that this measurement tool is best-suited for assessing the QoL of persons with aphasia [49]. Furthermore, it has been used successfully in persons with PPA [50]. For the present study, the SAQOL-39 seemed more suitable than the Aachen Life Quality Inventory used by Corsten et al. (2015), as it has a higher psychometric quality in comparison.

As a secondary outcome, depression will be measured by using the MADRS [39]. With the intention of not assessing persons with PPA “to destruction” [51], the MADRS was also chosen because it is an indirect method. The MADRS is a reliable and valid instrument, with high values indicating higher levels of depression [39].

In addition, the Satisfaction With Life Scale (SWLS, [52]) will be used as a scale to measure global life satisfaction. The SWLS has been shown to have good psychometric properties, including high internal consistency, and is less influenced by positive affect [52]. As the SWLS comprises only five items, it can be carried out quickly, and so it is presumably not an additional burden for persons with PPA.

The MMSE [37] will be used to measure cognitive functioning. On the one hand, this is important to ensure the inclusion criteria, and on the other hand, the progression of PPA over the course of the study period will be monitored. In clinical and research settings, the MMSE is the most widely used short cognitive test. It is reliable and valid with little effect on practice [37].

The scenario test (ST, [53]) measures participants’ communicative abilities and consists of 18 items (e.g., shopping or visiting a doctor). Due to the facilitated role-plays, the process is very close to realistic everyday communication. Recent evidence suggests that this method is well applicable to persons with PPA [54].

The Visual Analog Scale (VAS, [55]) will be administered before and after the first and fifth individual therapy sessions as well as before and after the first and fifth group therapy sessions. In contrast to the VAMS, which was used in the study of Corsten et al. (2015), the VAS consists of a single horizontal line instead of a vertical line and is bipolar, similar to the preceding scales of Stern et al. (1997, [22]). The VAS is a widely accepted scale that was adapted for various clinical questions examining pain or the effects of interventions, with special reference to QoL. However, to the best of our knowledge, the VAS, according to Ushijima et al. (2006), has neither been validated nor used for the evaluation of mood in persons with primary progressive aphasia.

After each individual-therapy session and each group-therapy session, the SLT will fill out a fidelity checklist, which is intended to record how well the SLT adheres to the adapted biographic-narrative Cope PPA manual. The checklist contains the basic principles of the biographic-narrative approach (e.g., resource-oriented attitude/nondirective communicative behaviour). For the SLT, the fidelity checklist will serve as a self-reflection tool (see Additional Supplementary Materials File S4). All assessment appointments as well as all therapy sessions will be recorded by video to evaluate procedures such as the MADRS and the ST afterwards by an independent rater. Similar to the randomised controlled pilot study by Volkmer et al. (2023) [16,56], a random sample of 10% of the videos of the individual- and group-therapy sessions will be evaluated by an independent rater to assess fidelity too (see Additional Supplementary Materials File S5). Thus, the quality of the treatment will be recorded.

In addition to the quantitative evaluation, semistructured interviews will be conducted by an independent rater, with all participants and their caregivers asking for experiences during the intervention or results of participation. Participants’ perceptions will complement the quantitative evaluation. We will use field notes to capture the content of the interviews. An overview of all measurements is given in Table 1.

#### 2.4.2. Data Management

All personal information will remain confidential. The data will be stored at the University Hospital Mainz only. Only members of the research team ([name], [name], [name], [name]) will have access. Participants will be assigned a unique code (see “Randomisation” above), which will be on the assessment sheets, in the names of the video files, and in the analysis of documents and publications. The list of participant names and their unique codes will be kept in a locked cabinet in the rooms of the outpatient memory clinic.

#### 2.4.3. Data Analysis

Qualitative data analysis will be carried out using MAXQDA (VERBI Software, 1989–2021); quantitative data analysis will be carried out using the statistical software SPSS (version 27, IBM^®^) and RStudio (2023.09.1 Build 494).

The data from ‘phase one’ will be analysed via qualitative content analysis by Elo and Kyngäs (2008, [62]). The video material of the focus group interview will be transcribed according to the content semantic transcription by Dresing and Pehl (2018) by two SLTs [63]. The coding process will be carried out by two SLTs. Categories will be formed deductively. The category system for the analysis will contain categories such as ‘characteristics of good therapy’/‘Augmentative and Alternative Communication’/‘coping strategies’/‘opinion on therapy materials’.

The quantitative data of ‘phase two’ will be analysed descriptively and inferentially. Before the inferential analysis, the normal distribution will be checked in both groups using the Shapiro–Wilk test in conjunction with a Q–Q plot and values of skew and kurtosis [64]. For the primary outcome of QoL, analysis of variance (ANOVA) will be used to calculate the point and mean values (before–after and therapy-waiting group comparisons). In addition, the dependent structure of the data will be examined using the intraclass correlation coefficient (ICC). To analyse the individual cases, the critical difference between the test procedures used will be determined. Recruitment, participation, fidelity, and reasons for drop-outs or missing data will be documented using descriptive statistics.

Semistructured interviews of ‘phase two’ will also be transcribed according to the content semantic transcription by Dresing and Pehl (2018, [63]) and analysed according to the qualitative content analysis by Elo and Kyngäs (2008, [62]). The category system for the analysis will contain categories such as ‘general conditions’, ‘content’, ‘materials’, ‘evidence of improvements in QoL’, or ‘evidence of identity work’.

Quantitative analysis is performed as both a per-protocol and intention-to-treat analysis to maximise external and internal validity while minimising statistical bias to maximise external and internal validity while minimising statistical bias. Complete drop-outs will be treated differently from missing values (e.g., due to an individual’s absence in individual or group therapy sessions in which a VAS was conducted). In these individual cases, imputation is considered. There are no plans to promote the retention of participants or intentions to follow-up in the case of individuals who drop out or deviate from the intervention protocol. There is no interim analysis planned.

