Persons with pronounced cognitive deficits, corresponding to a score < 10 out of 30 points in the established cognitive screening test Mini Mental-State Examination (MMSE, [37]), will be excluded at the beginning of the efficacy study, as there are indications from the literature that more complex questionnaires cannot be answered in cases of severe cognitive impairment [38]. Individuals whose cognition deteriorates to <10 points on the MMSE over the course of the study will not immediately be excluded. In these cases, an individual decision will be based on clinician ratings and according to the participants’ wishes.

Furthermore, the presence of severe depressive symptoms (clinical diagnosis and/or severe depressive symptoms, corresponding to >35 points on the Montgomery–Åsberg Depression Rating Scale (MADRS, [39]) is defined as an exclusion criterion at the beginning of the study because narraktiv was developed for preventing the occurrence of depression and has not been evaluated for the treatment of this condition [19]. However, due to the positive effects of participating in peer support groups on depression, persons with mild to moderate depression will not be excluded from the present study [40]. If participants show signs of depression in the course of the study (MADRS > 35 at t1–t3 or characteristics of a depressive disorder such as physical exhaustion, appetite disorders, changes in gestures/facial expressions or physiognomy during the therapy sessions), suicidal tendencies will be explored and documented in an individual setting. Questions from the national guideline “Unipolar depression” will be used for this purpose, e.g., “Have you had or do you have concrete plans to harm yourself?” and “Is there anything that keeps you alive?” [23]. If acute suicidal behaviour is suspected, an emergency psychiatric counselling will be conducted at the Department of Psychiatry and Psychotherapy of the University Hospital Mainz. If there is no acute suicidal tendency, the person will be promptly seen by a specialist in the outpatient memory clinic and the research team will plan further treatment steps if necessary. Participation in the study will be in addition to any other treatment participants may receive.

Whether persons with PPA previously received or currently receive speech and language therapy will not be a criterion for inclusion or exclusion in our study.

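### An intention-to-treat analysis is promised, but no follow-up is intended for people who drop out or deviate, so its result risks resting mainly on those who stayed

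*Protocol article*

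**What the plan says.** Protocol article, section 2.4.3 (Data Analysis), on the analysis sets: "Quantitative analysis is performed as both a per-protocol and intention-to-treat analysis". The stated purpose includes minimising bias. The same paragraph then says:

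- On gaps in the data: "Complete drop-outs will be treated differently from missing values (e.g., due to an individual’s absence in individual or group therapy sessions". The example given is a session at which a VAS was due. The next sentence reads "In these individual cases, imputation is considered". How complete drop-outs are handled is not said.
- On follow-up: "There are no plans to promote the retention of participants or intentions to follow-up in the case of individuals who drop out or deviate". The sentence goes on to name the intervention protocol as what is deviated from.

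Earlier in section 2.4.3, the primary method is given as "For the primary outcome of QoL, analysis of variance (ANOVA) will be used to calculate the point and mean values", for before–after and therapy-versus-waiting comparisons. On losses, it says that "reasons for drop-outs or missing data will be documented using descriptive statistics".

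Other sections bear on this:

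- Section 2.4 (Measurements) schedules assessments of all phase-two participants at t0, t1, t2 and t3, ten weeks apart.
- Section 2.4.5 makes the between-group criterion a greater SAQOL-39 improvement from t0 to t1 in the therapy group.
- Section 2.4.6 provides for therapy to be stopped if it is judged harmful.
- Section 2.1 says: "Individuals whose cognition deteriorates to <10 points on the MMSE over the course of the study will not immediately be excluded". It leaves those cases to an individual decision.

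**The concern.** An intention-to-treat analysis is meant to include people who stop or deviate. Stating that these people will not be followed up removes the data the analysis needs. This is a stated rule, not a detail left for later: an analysis plan can name an imputation model, but it cannot recover outcomes that nobody set out to collect.

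Two features make the loss potentially informative and unequal. Therapy may be stopped because it is doing harm, and such participants may well have poorer quality of life. And between t0 and t1 only the therapy arm has therapy to stop or deviate from, because the waiting group starts after ten weeks (section 2.3.3). That interval is the one on which the between-group success criterion rests. With 12 per arm (section 2.3.4), one or two people can move an arm mean noticeably.

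**Working it through.** **1. The passages side by side.** Section 2.4 says every phase-two participant is assessed at all four times. Section 2.4.3 says there is no intention to follow up people who drop out or deviate. For someone who stops therapy before t1, the two give different answers to whether the t1 assessment is sought.

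**2. What happens to such a person in the analysis.** The t0–t1 change needs both values. A participant with t0 only enters the ANOVA only if t1 is imputed. Imputation is attached, on the natural reading, to the sporadic gaps named just before it, and complete drop-outs are set apart from these. No stated route therefore brings an early drop-out into the t0–t1 contrast. A participant lost after t1 still contributes to that contrast if it is analysed on those two visits, so for this criterion the problem is loss before t1.

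**3. The plan's own figure.** Section 2.3.5 gives N = 24 for f = 0.275 (d = 0.55), α = 0.05 and power 0.8. It is reproducible as a repeated-measures within–between interaction with 2 groups, 3 measurements and correlation 0.5 (the last two are my assumptions):

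λ = f²·N·m/(1 − ρ) = 0.275² × 24 × 3 / 0.5 = 10.89, df = 2 and 44, power 0.822.

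Other settings also give 24 (for example 2 measurements with correlation 0.6). The section states no allowance for drop-out. I use only d = 0.55 from it, as a yardstick.

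**4. Size of a possible shift.** The article gives no drop-out rate and no outcome for those who leave, so both are assumed. Let k of the 12 in one arm be lost, with a mean change g SD below the full-arm mean, and none lost in the other arm. The mean of those remaining then shifts upward by

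shift = k·g/(12 − k).

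| g (SD) | k = 1 | k = 2 | k = 3 |
|---|---|---|---|
| 0.25 | 0.25/11 = 0.02 (4%) | 0.50/10 = 0.05 (9%) | 0.75/9 = 0.08 (15%) |
| 0.5 | 0.5/11 = 0.05 (8%) | 1.0/10 = 0.10 (18%) | 1.5/9 = 0.17 (30%) |
| 1.0 | 1/11 = 0.09 (17%) | 2/10 = 0.20 (36%) | 3/9 = 0.33 (61%) |

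Percentages are shares of d = 0.55. Because g is measured from the full-arm mean, the gap between those lost and those remaining is larger: g × 12/(12 − k), which is 1.33 SD at k = 3 and g = 1. The bottom-right cell is therefore an extreme case. If both arms lose the same number with the same gap, the two shifts cancel in the difference.

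**The case against.** A reader might infer that the intention-to-treat analysis simply becomes a completer analysis and that it coincides with the per-protocol set. The article does not say this. Drop-outs are to be treated differently, by a method left open that an analysis plan may supply, and the reference of the imputation sentence is somewhat ambiguous. Missed sessions count as missing values, so an imperfect attender who is assessed at t1 can be in the intention-to-treat set and outside the per-protocol set. The two sets need not be identical.

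A reader might also infer that the bias must favour Cope PPA. That is not shown. Waiting participants can leave too. The Discussion notes that declining awareness of deficits could itself accompany better quality of life, so those who progress need not rate themselves lower on SAQOL-39.

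Nor should section 2.1 be read as a rule for removing participants whose MMSE falls below 10. It says they are not excluded at once, and the individual decision rests on clinician ratings and the participant's wishes.

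All three limits stand. What survives is the stated absence of any intention to follow up, set against a promised intention-to-treat analysis and a schedule that covers everyone.

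**Conclusion.** The point holds as an unreconciled conflict between sections 2.4 and 2.4.3, with a resulting risk to the intention-to-treat analysis. As the text stands, outcomes after stopping or deviating may not be sought, and nothing stated brings early drop-outs into the t0–t1 comparison. Bias towards the therapy arm is plausible but not certain.

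The size is unknown. The table's range, from negligible to more than half the planning effect, rests on an assumed number lost, an assumed gap and loss confined to one arm. It shows how sensitive a 12-per-arm comparison is and is not a forecast. The point is worth settling before assessments begin, because outcomes not collected then cannot be recovered reliably.

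**What to change.** Reconcile sections 2.4 and 2.4.3 by replacing the no-follow-up sentence with wording such as: all randomised participants, including those who stop or deviate from therapy, are invited to the remaining scheduled t1–t3 outcome assessments unless they withdraw consent or do not meet the capacity check that section 2.1 requires before each assessment.

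For the analysis:

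- Analyse participants as allocated, with a method that uses all available visits, for example a likelihood-based mixed model.
- Add a sensitivity analysis in which those lost are assumed worse by stated amounts.
- Keep the per-protocol analysis as supportive.
- Leave the decision on participants who fall below MMSE 10 with the clinicians, as section 2.1 does, and state how their outcomes enter the intention-to-treat analysis.

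The cost is a change of wording and some extra contact effort; the assessments are already in the schedule.
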